
### Power and Sample Size

We plan to conduct a prospective multicentric observational study to investigate the prevalence and severity of mental illness symptoms and fatigue in individuals with long COVID. Based on previous studies and expert opinion, we expect the prevalence of fatigue and mental symptoms in this population to be around 50% [42,43]. We aim to detect a minimum effect size of 0.2 with a power of 80% and a significance level of *P=.*05.

Using these assumptions, we performed a sample size power analysis using a 2-sample *t* test. We found that a total sample size of 200 participants (100 with adverse mental health symptoms and 100 without) would be required to detect the minimum effect size of 0.2 with 80% power and a significance level of *P=*.05. The required sample size was calculated using an a priori power analysis with an online calculator [44]. To compensate for a projected 25% loss to follow-up, we aimed for 250 participants.

We plan to recruit participants from multiple hospitals and primary care centers across Portugal, focusing on individuals who have been diagnosed with long COVID and are experiencing mental illness symptoms and/or fatigue. Recruitment will be closely monitored throughout the study to assess the pace at which participants are enrolled. The need for sample size adjustment will be determined based on the observed recruitment rates and the accumulating data. We plan to conduct an interim analysis after the recruitment of the first 100 patients.

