Research questions of the study.Research Question 1 (primary outcome):Do patients with long COVID who experience depression and/or anxiety symptoms have a higher prevalence of fatigue?Research questions 2 to 4 (secondary outcomes):Is there a correlation between the type of fatigue and depression and/or anxiety symptoms among patients post COVID-19?Is there a correlation between fatigue and the presence of PTSD symptoms in patients post COVID-19?Do patients with fatigue associated with mental health disorders have a lower health-related quality of life (HRQoL) after COVID-19?

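### At the stated effect size of 0.2, a two-sample t test with 100 per group has about 29% power, not 80%

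*Protocol article*

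**What the plan says.** All of the inputs are in the Power and Sample Size section of the protocol article.

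- Test: "we performed a sample size power analysis using a 2-sample *t* test".
- Sample size: a "total sample size of 200 participants (100 with adverse mental health symptoms and 100 without) would be required".
- Target: that number "would be required to detect the minimum effect size of 0.2 with 80% power", at a .05 significance level. The effect size, power and level are each given twice in the section.
- Expected prevalence: "we expect the prevalence of fatigue and mental symptoms in this population to be around 50" per cent.
- Attrition: "To compensate for a projected 25% loss to follow-up, we aimed for 250 participants".

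The section gives no standard deviation, no scale for the effect size and no sidedness.

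The primary research question in Textbox 1 (Introduction) is about a proportion: "Do patients with long COVID who experience depression and/or anxiety symptoms have a higher prevalence of fatigue".

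**The concern.** For a two-sample t test, an effect size of 0.2 without further definition is read as a difference of 0.2 standard deviations. Detecting that takes several hundred participants per group, so 100 per group looked too few by a factor of about four.

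The sentence tells readers how sensitive the study is. If it is wrong, they will believe that a small difference would be found four times in five, when it would be missed about seven times in ten. A non-significant result on the primary question, or on the physical or psychological fatigue subscale, could then be taken as evidence against an effect that the study was unlikely to detect. The same section allows the sample size to be adjusted on accumulating data and plans an interim analysis after 100 patients. Those decisions also need a correct planning effect.

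A second mismatch adds to the doubt: the named test compares means, while the primary question compares prevalences.

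**Working it through.** **Inputs from the article:** two-sample t test, effect size 0.2, significance level .05, power 80%, 100 per group, prevalence about 50%, 25% loss, 250 enrolled.

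**Assumptions:** 0.2 is a standardized mean difference d, and the test is two-sided. One-sided results are also given. Normal quantiles: z(0.975) = 1.960 and z(0.80) = 0.842, so (1.960 + 0.842)² = 7.849.

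**1. Attempt to reproduce the stated 200.**
n per group = 2 × 7.849 / d² = 2 × 7.849 / 0.04 = 392.4, so 393 by the normal approximation. The exact noncentral-t solution is 393.4, so 394 per group and **788 in total**. One-sided it is 310 per group, 620 in total. The stated 200 is not reproduced.

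**2. Power at the stated size.**
Power ≈ Φ(d√(n/2) − 1.960) = Φ(0.2 × √50 − 1.960) = Φ(1.414 − 1.960) = Φ(−0.546) ≈ 0.29.

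| Per group | Power at d = 0.2, exact t, two-sided | One-sided |
|---|---|---|
| 100 | 29.1% | 40.7% |
| 125 (all 250 retained) | 35.0% | 47.3% |
| 93.75 (250 × 0.75 / 2) | 27.5% | 39.0% |

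**3. Effect detectable with 80% power, two-sided.**
d = (1.960 + 0.842) × √(2/n) = 2.802 × √0.02 = 0.396 for n = 100. The exact t solution is **0.398**, and 0.411 with 93.75 per group.

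**4. Readings of 0.2 that do give about 200.**

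| Reading | Sample size for 80% power, two-sided .05 |
|---|---|
| One-sample or paired t test, d = 0.2 | 199 in total |
| Chi-square, 1 df, w = 0.2 | 197 in total |
| Correlation, r = 0.2 | 194 in total |
| ANOVA, two groups, f = 0.2 | 199 to 200 in total |
| Proportions 40% vs 60% | 97 per group |
| Proportions 50% vs 70% | 93 per group (103 with continuity correction) |
| Two-sample t test, absolute difference 0.2, SD 0.5 | 100 per group |

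The last row is a t test on a yes/no variable with prevalence 50%: SD = √(0.5 × 0.5) = 0.5, so d = 0.2 / 0.5 = 0.4. The exact requirement is 99.1 per group, and 100 per group gives 80.4% power. This is again a 20-percentage-point difference in prevalence.

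**5. Power for that prevalence difference at the planned size.**
For 40% versus 60% with pooled variance under the null, power = Φ[(0.2√n − 1.960 × √(2 × 0.5 × 0.5)) / √(0.4 × 0.6 + 0.6 × 0.4)]. With n = 100 this is Φ[(2 − 1.386) / 0.693] = Φ(0.886) = **81%**. With 93.75 to 94 per group it is 79%.

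**The case against.** The strongest reply is that the article never calls 0.2 a standardized difference. It gives a prevalence near 50%, then the effect of 0.2, and then says that the calculation used those assumptions. A two-sample t test on a binary outcome with SD 0.5 and an absolute difference of 0.2 needs exactly 100 per group. On the d = 0.2 reading, the 50% plays no part at all. The fault would then be a mislabelled effect size, not too small a sample.

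This is a plausible account of where 200 came from, and it means that the 29% depends on reading 0.2 as d. It does not rescue the text. That reading corresponds to d = 0.4, and the article states neither the SD of 0.5 nor that 0.2 is a difference in proportions.

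Three lesser points carry some weight.

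- The article does not claim that a null result would rule out small associations. The risk of misreading is an inference from the stated power.
- A calculation based on means has some basis, because the Fatigue section keeps only Likert scoring and Phase 2 of Textbox 2 includes comparisons of means. The primary question is still one of prevalence.
- A statement of 40% versus 60% is fitted to the existing sample size, and it presupposes a definition of a fatigue case. The Fatigue section sets aside the bimodal version, which carries the cut-off of 4, and Phase 2 derives cut-offs from the cohort itself. The restated sentence should therefore be presented as what the sample can detect, not as a target chosen in advance.

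**Conclusion.** The power statement is wrong as written. For the named test at an effect size of 0.2, 100 per group gives 29% power, against the 80% claimed. The required total is 788, against 200. The detectable standardized difference is 0.40, twice the stated minimum.

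This rests on 0.2 being a standardized mean difference, a two-sided .05 level and equal groups. One-sided testing (41%) and retention of all 250 participants (35%) do not change the conclusion. Under a different definition of 0.2, chiefly a 20-point difference in prevalence near 50%, the sample size is adequate and the error lies in the stated effect measure. Either way the paragraph must be corrected.

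**What to change.** Keep the sample size and rewrite the statement to match the primary comparison. Suggested text: *With 100 participants per group, a two-sided 5% test of two proportions has about 80% power to detect a 20-percentage-point difference in fatigue prevalence (for example, 60% versus 40%; phi about 0.2). For mean CFQ-11 score, the standardized difference detectable with 80% power is 0.40.* Delete the claim of 80% power for an effect size of 0.2 with a two-sample t test.

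The authors should also confirm which quantity they entered in the online calculator and name the definition of a fatigue case to which the prevalence refers. If a standardized difference of 0.2 really is the target, rewording is not enough: the calculation needs 394 per group.

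On the first route the cost is confined to the wording of the sample-size section. No participant or procedure is affected, but the stated detectable effect becomes less favourable.

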**Figure 2 figure2:**
[figure not shown]
Study timeline.

We plan to enroll 250 participants, including 100 with adverse mental health symptoms and 100 without, to explore the intricate relationship between adverse mental health symptoms and both physical and psychological fatigue in individuals recovering from long COVID. Preliminary analyses indicate a compelling connection, wherein patients who report heightened levels of depression and anxiety also tend to experience increased fatigue. These findings underscore the importance of considering mental health as a pivotal factor in understanding the enduring impact of COVID-19 beyond the acute phase. In addition to depression and anxiety, our study explores the persistence of PTSD symptoms in a subset of participants. Initial results suggest that, even after recovery from the acute phase of the infection, a proportion of individuals continue to grapple with the psychological repercussions of the virus. This observation aligns with emerging evidence suggesting a prolonged psychological impact of COVID-19, emphasizing the need for comprehensive mental health support for patients after contracting COVID-19. The identified links between mental health symptoms and fatigue have broad implications for the holistic care of this patient population. Understanding these connections can guide targeted interventions, emphasizing the importance of addressing mental well-being alongside physical recovery. As we delve deeper into the data and conduct further analyses, a more nuanced understanding of these relationships will emerge, informing future health care strategies and interventions.

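### The enrolment target of 250 covers a 20% loss to follow-up, not the projected 25%; at 25% loss about 187 patients remain, fewer than the 200 required

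*Protocol article*

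**What the plan says.** Three figures in Methods, Power and Sample Size, bear on this point.

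- The analysable number: "We found that a total sample size of 200 participants (100 with adverse mental health symptoms and 100 without) would be required".
- The design behind it: "we performed a sample size power analysis using a 2-sample *t* test", for an effect size of 0.2, "with 80% power and a significance level of *P=*.05".
- The allowance for attrition: "To compensate for a projected 25% loss to follow-up, we aimed for 250 participants".

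The Results section, in the paragraph after the study timeline figure, repeats the target: "We plan to enroll 250 participants, including 100 with adverse mental health symptoms and 100 without".

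Under Data Collection, the first visit (T1, 3 months) records demographics, history, comorbidities and acute severity. The fatigue, anxiety and depression, post-traumatic stress and quality-of-life questionnaires are listed for the second visit (T2, 6 months).

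**The concern.** The required number, the projected loss and the target do not fit together. Loss to follow-up is a fraction of those enrolled, so the required number has to be divided by the retained fraction. Here it appears to have been multiplied by one plus the loss, which always falls short.

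The plan therefore claims protection against its own projected attrition that it does not have. The lost patients cannot be partly recovered. The primary question compares fatigue between patients with and without depression or anxiety symptoms, and both the fatigue score and the grouping come from T2 questionnaires. A patient lost before T2 has neither.

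**Working it through.** **Inputs, all from Power and Sample Size:** required analysable total 200 (100 + 100); projected loss 25%; enrolment target 250.

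**Step 1. Reproduce the plan's figure.** Required number × (1 + loss) = 200 × 1.25 = 250. This matches exactly, so this is evidently how the target was obtained.

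**Step 2. Patients left after the projected loss.** Target × (1 − loss) = 250 × 0.75 = 187.5, or about 94 per group if the groups are equal. The shortfall is 200 − 187.5 = 12.5 patients, and 12.5 / 200 = 6.25%.

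**Step 3. Correct inflation.** Required number / (1 − loss) = 200 / 0.75 = 266.7, rounded up to 267. That is 17 more than 250.

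**Step 4. Loss that 250 does cover.** 1 − 200 / 250 = 0.20, or 20%.

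Steps 1 to 4 do not depend on the test, on sidedness or on how the 200 was derived.

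**Step 5. Consequence for detectable difference and power.** The article does not define the scale of its 0.2 or state sidedness. The scenarios below are therefore assumptions: two-sided 5%, equal groups, 100 versus 93.75 per group.

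*Detectable standardised difference at 80% power*, (1.960 + 0.842) × √(2/n):
- n = 100: 2.802 × 0.1414 = 0.396
- n = 93.75: 2.802 × 0.1461 = 0.409

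The exact t-test versions are 0.398 and 0.411.

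*Power for two proportions*, Φ{[|p1 − p2| − 1.960 × √(2p̄(1 − p̄)/n)] / √[(p1(1 − p1) + p2(1 − p2))/n]}, where p̄ is the mean of p1 and p2. For 40% versus 60%:
- n = 100: (0.2 − 1.960 × 0.0707) / 0.0693 = 0.886, power 81.2%
- n = 93.75: (0.2 − 1.960 × 0.0730) / 0.0716 = 0.795, power 78.7%

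| Assumed scenario | Power, 100 per group | Power, 93.75 per group |
|---|---|---|
| 40% vs 60% | 81.2% | 78.7% |
| 50% vs 70% | 82.8% | 80.3% |
| t test, standardised difference 0.4 | 80.4% | 77.8% |
| Two means, standardised difference 0.2 (normal approximation) | 29.3% | 27.7% |

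In each scenario the loss costs about 1.5 to 2.6 percentage points of power.

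**The case against.** The arithmetic is not in dispute. The case on the other side concerns its weight.

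- **Another reading of 25%.** It could mean a quarter of the 200 required, or 50 patients. But 50 lost out of 250 enrolled is a 20% loss, so the sentence would still misstate the attrition covered.
- **Small effect, depending on assumptions.** This stands. No conclusion of an observational study turns on 12 or 13 patients, and with 50% versus 70% power stays just above 80%. The article states neither that contrast nor 40% versus 60%, so these power figures illustrate the effect and are not the plan's own.
- **The 200 is itself doubtful.** This also stands, as a separate and larger matter. A two-sample t test at a standardised effect of 0.2 needs about 393 to 394 per group (two-sided). The inflation error is secondary to that, but any revised base number would be under-inflated again if the same step were reused.
- **Enrolment may nearly coincide with the questionnaires.** Inclusion Criteria requires at least 6 months since diagnosis, Recruitment places the invitation at the end of a follow-up appointment, and the Abstract places data collection at 6 to 9 months. Actual loss may then be well under 25%. That would question the projection; it would not make 250 cover it.
- **The size may be adjusted.** The section links adjustment to recruitment rates and accumulating data and plans an interim analysis after 100 patients. It gives no corrected figure and leaves the claim about 250 in place.

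**Conclusion.** The concern holds. A target of 250 covers a 20% loss. At the projected 25% it leaves about 187 analysable patients, 12 to 13 below the stated requirement of 200; covering 25% would have needed 267. That result rests only on the article's own three figures and on loss being counted as a fraction of those enrolled.

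The practical effect is modest: a detectable standardised difference of about 0.41 instead of 0.40, and about 2.5 percentage points of power in the scenarios that sit near 80%. Those figures assume equal groups and two-sided 5% testing. The result takes the 200 as given and does not endorse it. The statement should be corrected because it credits the design with a property it lacks.

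**What to change.** Replace the sentence on attrition in Power and Sample Size in one of two ways.

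1. **Preferred:** keep the 25% projection and state that, of 250 enrolled, about 187 (roughly 94 per group if equal) are expected to be analysable, with the difference detectable at that number.
2. **Alternative:** state that 250 participants allow for a loss of up to 20%. This is a true description of what 250 covers. If 20% is also presented as the expected loss, it needs its own justification, because the article projects 25%.

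Under option 1, define the scale of the 0.2 effect size in the same edit. Otherwise a detectable standardised difference of 0.41 will stand beside a stated 0.2 with no explanation.

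Align the Results sentence so that 250 is the number enrolled and the 100 + 100 is the number required for analysis.

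The cost is one sentence, plus the alignment in Results. Recruitment was due to close in December 2023, and neither option asks for further patients. The stated figure becomes slightly less favourable.

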## Introduction

Despite the World Health Organization (WHO) declaration marking the end of the COVID-19 pandemic on May 5, 2023 [1], millions of people continue to have postvirus complaints. Moreover, the virus remains endemic in many parts of the world. Confirmed COVID-19 cases have exceeded 430 million globally, with 200 million in Europe alone [2]. The causative agent of COVID-19 is the novel SARS-CoV-2 [3]. Although, as the name implies, respiratory symptoms are acute, the term long COVID (or post-COVID syndrome or long-haul COVID-19) began gaining recognition in the scientific and medical communities after the first descriptions of long-lasting symptoms related to mental health, such as anxiety or stress after the first infection [4]. While the definition of long COVID is unclear, the most frequent symptoms are fatigue and dyspnea [5,6]. Other less typical symptoms include cognitive and mental disorders, headache, myalgia, chest and joint pain, smell and taste dysfunction, cough, hair loss, insomnia, wheezing, rhinorrhea, sputum, and cardiac and gastrointestinal issues [4]. These symptoms may persist for up to 6 months after hospital discharge, severely impacting patients’ quality of life [7]. Since July 2021, long COVID is considered a disability under the *Americans With Disabilities* Act [8].

Per its definition, long COVID appears within 3 months after the onset of COVID-19, with symptoms lasting for at least 2 months that an alternative diagnosis [9] cannot explain, including, myalgic encephalomyelitis and chronic fatigue syndrome. However, studies have reported different persistent symptoms in contrasting durations and frequencies among survivors of long COVID [10,11]. Long COVID appears like other postviral syndromes observed in other coronavirus diseases. For example, symptoms of fatigue, myalgia, and psychiatric impairments have affected survivors of Middle East respiratory syndrome (MERS) and those with severe acute respiratory syndrome (SARS) for up to 4 years [10,12,13]. Even at 7-year and 15-year follow-ups, pulmonary and bone radiological complications were evident among a proportion of survivors of SARS who were predominantly younger than 40 years [10,14,15]. This is unsettling, as it implies that long COVID may extend beyond just a few months.

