### Recruitment

Our study will be conducted in 1 private and 4 public Portuguese hospitals that have established follow-up post–COVID-19 medical consultations. Patients who meet the eligibility criteria will be invited to participate in the study at the end of their appointments in the follow-up clinics. This study will be conducted using a consecutive, nonrandom sampling technique.

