### Inclusion Criteria

Patients who cumulatively meet the following criteria will be eligible for inclusion: (1) ≥18 years; (2) previous case of COVID-19 at least 6 months after the diagnosis that is duly documented in the clinical record; (3) persistent symptoms after COVID-19 recovery, as defined by the WHO [9]; and (4) SARS-CoV-2 RNA confirmed by a positive real-time reverse-transcription polymerase chain reaction (RT-PCR) on a nasopharyngeal swab or SARS-CoV-2 antigen confirmed with a nasopharyngeal swab by a health care professional within 7 days of initial symptoms.

We will implement multiple measures to exclude the possibility of second infections and ensure that the individuals included have persistent symptoms following their initial COVID-19 recovery. Our inclusion criteria stipulate that individuals must have a positive test result for SARS-CoV-2 RNA or antigen within 7 days after their initial infection. Additionally, we will conduct thorough reviews of medical records and clinical assessments to assess symptom presentation and timing, differentiating between persistent cases and new infections. In cases of uncertainty or potential overlap with new infections, we are prepared to conduct repeat testing, which may include RT-PCR and genomic sequencing for accurate classification.

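### The stated recruitment focus on patients with mental symptoms and/or fatigue contradicts consecutive enrolment and, so far as it is applied, biases the primary association downward

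*Protocol article*

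**What the plan says.** Research Question 1, in the Introduction (Textbox 1), asks: "Do patients with long COVID who experience depression and/or anxiety symptoms have a higher prevalence of fatigue". Depression or anxiety symptoms are therefore the exposure, and fatigue is the outcome.

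The article describes recruitment in two ways.

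- **Recruitment, Inclusion Criteria, Exclusion Criteria.** Eligible patients are invited at the end of follow-up appointments: "This study will be conducted using a consecutive, nonrandom sampling technique". The symptom criterion is "persistent symptoms after COVID-19 recovery, as defined by the WHO". Neither fatigue nor mental symptoms is required, and no exclusion criterion removes a patient for lacking both. The Introduction names other lasting complaints, among them "headache, myalgia, chest and joint pain, smell and taste dysfunction, cough, hair loss", so a patient can qualify with neither.
- **Power and Sample Size.** Recruitment is described as "focusing on individuals who have been diagnosed with long COVID and are experiencing mental illness symptoms and/or fatigue".

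The Power and Sample Size section also expects fatigue and mental symptoms to have a prevalence of about 50%, and plans 100 participants with and 100 without adverse mental health symptoms. Under Data Collection, the fatigue scale (CFQ-11) and the anxiety and depression scale (HADS) are completed at the second visit (T2).

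**The concern.** The second description selects patients on exposure or outcome. Someone without mental symptoms who is recruited under it is there because of fatigue. That thins out one cell of the primary two-by-two table, the patients with neither complaint, and raises fatigue prevalence in the comparison group. The bias runs against the association that the study expects to find, and it can be large enough to change the sign.

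The two descriptions cannot both be the enrolment rule, and a reader of the results could not tell which one produced the sample. The Limitations section mentions only that more severely affected people may be less willing to take part, which is a different mechanism. The five analysis phases in Textbox 2 contain nothing that would show which rule applied.

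**Working it through.** The plan gives no figure for this selection, so there is none to reproduce. The sample size in the same section is a separate matter and is not used here, apart from its 100/100 split in step 4.

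**Inputs.** From the document: prevalence of about 50%, read as applying to fatigue and to mental symptoms separately. Assumed for illustration: the true fatigue prevalences, and *s*, the rate at which patients with neither complaint are enrolled relative to the other three cells (which are taken to be enrolled at equal rates).

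**Step 1, formula.** Let the cells be a (both), b (mental symptoms only), c (fatigue only) and d (neither). The true odds ratio is ad/(bc). Selection replaces d by s·d, so the observed OR = s × true OR. Fatigue prevalence with mental symptoms stays a/(a+b). Without them it becomes c/(c+s·d). The sign reverses when s < 1/(true OR).

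**Step 2, worked example.** Assume a true 60% v 40%. Per 100 patients, a = 30, b = 20, c = 20, d = 30, and OR = (30×30)/(20×20) = 2.25.

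- s = 0.5: without mental symptoms 20/(20+15) = 57.1%, so 60% v 57.1%; OR = 0.5 × 2.25 = 1.13.
- s = 0.25: 20/(20+7.5) = 72.7%, so 60% v 72.7%; OR = 0.25 × 2.25 = 0.56.
- Reversal below s = 1/2.25 = 0.44.

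**Step 3, range.** Both prevalences are held at 50%. Entries are fatigue prevalence with v without mental symptoms.

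| True | True OR | s = 0.5 | s = 0.25 | s = 0 | Reverses below s |
|---|---|---|---|---|---|
| 50% v 50% | 1.00 | 50% v 67% | 50% v 80% | 50% v 100% | 1.00 |
| 55% v 45% | 1.49 | 55% v 62% | 55% v 77% | 55% v 100% | 0.67 |
| 60% v 40% | 2.25 | 60% v 57% | 60% v 73% | 60% v 100% | 0.44 |
| 65% v 35% | 3.45 | 65% v 52% | 65% v 68% | 65% v 100% | 0.29 |
| 70% v 30% | 5.44 | 70% v 46% | 70% v 63% | 70% v 100% | 0.18 |

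**Step 4, is the strict case (s = 0) consistent with the plan?** Applied as an absolute rule, and with entry symptoms matching the T2 classification, all 100 participants without mental symptoms would have fatigue. If the 50% figures also described the recruited sample, the share with both would be 0.5 + 0.5 − 1 = 0. The strict reading does not fit the plan's own expectation.

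**Step 5, entry symptoms as an imperfect proxy.** The groups are formed at T2, not at invitation. A latent-normal simulation applied the focus strictly to entry symptoms that agree only partly with the T2 measures (assumed reliability 0.5, 0.7 or 0.9). Fatigue prevalence with v without mental symptoms was:

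| Assumed latent correlation | Unselected | Reliability 0.5 | 0.7 | 0.9 |
|---|---|---|---|---|
| 0.2 | 56% v 44% | 60% v 60% | 60% v 67% | 59% v 80% |
| 0.4 | 63% v 37% | 67% v 53% | 67% v 62% | 66% v 76% |
| 0.6 | 70% v 30% | 74% v 45% | 74% v 54% | 73% v 70% |

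The difference shrinks in all nine settings and reverses in three. Applying the focus loosely would soften this further.

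**The case against.** The strongest reply is that the sentence is loose description in a sample-size section, not an eligibility rule. It speaks of a focus, not a restriction. The operative sections admit any persistent symptom, the Abstract enrols symptomatic adults attending follow-up, and Data Collection has a letter going to all discharged patients. The same sentence also mentions primary care centers, whereas the Recruitment section names only hospitals, which suggests careless wording. The Results section reports that preliminary analyses show more fatigue in patients with more depression and anxiety, which is hard to square with an emptied cell or a reversed sign.

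Most of this stands. A reader might infer that the group with neither complaint is missing by design, or that no analysis could repair the comparison. The documents do not support either inference. The formal criteria admit such patients and the scales are applied at T2. Textbox 2 also derives fatigue cut-offs within this cohort, so a patient who reports some fatigue at entry may fall below the cut-off.

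The reply does not remove the contradiction. Both descriptions are current text, and nothing says which governs. A positive preliminary association argues against strict application but is compatible with attenuation. Any relative rate below 1 pushes the association downward, whatever the true difference.

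**Conclusion.** The contradiction is real and concerns who enters the primary comparison. It should be fixed, with moderate confidence about its practical effect. To the extent that the focus on mental symptoms and/or fatigue was applied, patients with neither complaint are under-sampled and the association is biased downward. Whether it reverses depends on the relative sampling rate and the true effect. For an assumed true 60% v 40% the sign changes only below s = 0.44, so enrolling these patients at half the rate attenuates the difference to 60% v 57% without reversing it.

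Only the 50% prevalence comes from the document. The true differences, sampling rates, reliabilities and correlations are illustrative assumptions. A reader might take the 50% v 100% result as what the plan implies. It needs strict application, perfect agreement between entry symptoms and the T2 classification, and no true association, and the documents establish none of these.

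**What to change.** In Power and Sample Size, delete the clause on mental symptoms and fatigue. State that all consecutive attendees who meet the Inclusion and Exclusion Criteria are invited, regardless of fatigue or mental symptoms.

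The Results section gives December 2023 as the recruitment deadline, so a change to enrolment may come too late. In that case, report how patients were actually invited at each site. Where records show sites or periods with targeted invitations, repeat the primary comparison without them as a sensitivity analysis, and list the selection as a limitation. This depends on records of invitation existing; the article mentions collecting only reasons for declining.

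The cost is one sentence and, if enrolment is still open, a note to sites, after which more patients with neither complaint would enter. If enrolment is closed, the cost is a smaller sample in the sensitivity analysis.
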